### Study design

This randomized, single-blind, sham-controlled neuroimaging study will be conducted at the affiliated hospital of Chengdu University of Traditional Chinese Medicine (CDUTCM), China. A total of 60 CID patients with GI disorder will be recruited using advertisements on posters and hospital networks. All patients meeting the inclusion criteria will randomly receive either 20 sessions of real acupuncture treatment or 20 sessions of sham acupuncture treatment. A multimodal MRI examination and evaluation will be performed at both baseline and the end of treatment. Additionally, 30 healthy controls (HCs) matched for age, sex, and education level will receive one multimodal MRI scan and a clinical assessment. A flowchart of the trial design is shown in Fig. 1, and the participant timeline is shown in Fig. 2.

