**Fig. 2 Fig2:**
[figure not shown]
Time schedule of enrolment, interventions and assessments. Eligible patients will be screened according to inclusion and exclusion criteria. These patients will then sign an informed consent form and undergo a medical examination. Eligible insomniacs will be randomly assigned to either the true or sham acupuncture groups and complete clinical and MRI assessments before treatment. After a 4-week treatment period, these patients will undergo clinical and MRI assessments again. In addition, adverse events will be recorded in the CRFs at any time during treatment. MRI, magnetic resonance imaging; PSQI, Pittsburgh sleep quality index; GSRS, gastrointestinal symptom rating scale; SAS, self-rating anxiety scale; SDS, self-rating depression scale

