#### Inclusion criteria

Patients diagnosed with CID are eligible to participate in the study. Inclusion criteria are (1) aged between 18 and 65 years, right-handed, any gender; (2) meets the CID diagnostic criteria in the International Classification of Sleep Disorders-Third Edition (ICSD-3) [43], and meets the criteria for spleen and stomach disharmony syndrome in the Clinical Terminology of Traditional Chinese Medical Diagnosis and Treatment—Syndromes (GB/T 16751.2-1997) [44]; (3) Pittsburgh Sleep Quality Index score above 7 (PSQI score > 7); (4) not taking any medication or health care products to improve sleep quality and experienced GI diseases at least 2 weeks before study enrollment; (5) has not participated in other clinical trials within the last month; and (6) agrees to voluntarily participate in the study and signs an informed consent form.

The HCs must meet the following inclusion criteria: (1) passes the neuropsychological tests and reports good sleep quality; (2) no GI symptoms; (3) all physiological indexes within the normal range following a physical examination, and no previous functional or organic disease or head injury; and (4) agrees to voluntarily participate in the study and signs an informed consent form.

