### Concomitant medication

Patients will be advised to avoid medication as much as possible during the study. Following medical ethical principles, if patients’ insomnia symptoms do not significantly improve and they cannot tolerate their insomnia, they may temporarily take sleeping drugs. Except for sleeping drugs, other drugs will be not allowed to be used in the trial. Researchers will record the name, dosage, and time of the drugs taken in detail in the Case Report Form (CRF).

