### Multimodal MRI data acquisition

MRI examinations will be performed at the MRI Center at the University of Electronic Science and Technology of China using a 3.0 T MRI scanner (GE Discovery MR750, USA) equipped with a standard 8-channel head coil. MRI scans will be assessed at baseline and after 4 weeks. Subjects will be told to eat light food; avoid drinking strong tea, coffee, and wine; and avoid strenuous exercise the day before the scan. To prevent head movements affecting the image, foam pads and towels will be used to hold the head. During the MRI examination, all subjects will wear earplugs and be instructed to relax with their eyes closed and keep their heads clear. The scanning procedure produces a three-dimensional T1 image (3D-T1), a blood oxygenation level-dependent fMRI (BOLD-fMRI), a DTI sequence, and a proton ^1^H-MRS. The 3D-T1 scanning parameters will be as follows: repetition time (TR)/echo time (TE) = 5.988/1.972 ms, slice thickness = 1 mm, slice number = 154, field of view (FOV) = 256 × 256 mm. The BOLD-fMRI scanning parameters will be as follows: TR/TE = 2000/30 ms, flip angle = 90°, slice number = 35, matrix size = 3.75 × 3.75, FOV = 64 × 64 mm, slice thickness = 4 mm. The DTI data will be obtained using the following parameters: FOV = 240 × 240 mm, TR/TE = 6800/93 ms, matrix size = 128 × 128, and slice thickness = 3 mm with no gap. The proton ^1^H-MRS asymmetric PRESS sequence includes TE1 = 25 ms, TE2 = 85 ms, TR = 2 s, and a 2 × 2 × 2 cm area of interest on the anterior cingulate gyrus will be selected [29].

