#### Imaging data analysis

The fMRI data will be preprocessed and analyzed using SPM12 (http://www.fil.ion.ucl.ac.uk/spm/) and CONN toolbox 18b (https://web.conn-toolbox.org/) with MATLAB 2014b (MathWorks, Inc., Natick, MA, USA). The sMRI data will be analyzed using the VBM toolbox within SPM12. DTI data will be processed using FSL Software on Linux. MRS data will be preprocessed using the commercially available software LCModel spectral-fitting package (version 6.3-1 N; Stephen Provencher, Inc., Oakville, ON, Canada). After standard preprocessing of each imaging modality, the following brain activity information will be calculated to examine the neural response to different treatments: the amplitude of low-frequency fluctuation, group independent component analyses, seed-based functional connectivity, cortical thickness, tract-based spatial statistics, and Glu. Finally, Pearson correlation analysis will be used to assess the association between changes in multimodal neuroimaging features and improvements in clinical outcomes in each group. MRI data from patients who received the drugs will be excluded because of the effects of the combination on brain function during the trial.

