Multimodal MRI will provide technological data to examine the neuropathological mechanism underlying the effect of acupuncture on CID with GI disorder. We first want to explore neuropathological changes in patients with CID and GI disorder from the perspectives of brain structure, function, and metabolism. Our previous study was a preliminary exploration of the pathogenesis of insomnia (rather than CID with GI disorder) in terms of brain function and structure [23, 24, 67]. Other research teams have confirmed that insomnia patients have abnormal brain metabolism using MRS technology [27–29]. At present, there are no brain imaging studies on patients with CID and GI disorders. Most studies on insomnia have identified the abnormal brain regions in CID patients as the anterior cingulate gyrus, hippocampus, thalamus, and other regions [68, 69]; these brain regions also feature in GI imaging studies [70]. It remains to be determined whether the structure, function, and metabolism of these brain regions are also changed in CID with GI disorder. Second, we wish to explore the central response mechanism of acupuncture. There is evidence that acupuncture can regulate the neuroplasticity and functional connectivity of abnormal brain regions in other diseases [31, 71], but most studies have used only a single neuroimaging pattern and cannot fully explain the mechanism of acupuncture. Multimodal MRI provides a new way of exploring the mechanism underlying acupuncture. It can examine the mechanism of action in detail from multiple perspectives, which is a more comprehensive approach than the use of single-mode magnetic resonance technology. At present, multimodal MRI has been used to investigate the effect of acupuncture on depression, chronic fatigue syndrome, and other diseases [72–74]. In this study, we will use multimodal MRI combined with sMRI, fMRI, DTI, and MRS. Of these techniques, sMRI and DTI can detect structural changes in different brain regions, fMRI can explore changes in functional connections between different brain regions, and MRS can detect changes in different brain metabolites.

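### The drug-exclusion rule for MRI data names no scan, so as written it also removes pre-treatment baseline scans to which its stated reason cannot apply

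*Protocol article*

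**What the plan says.** All places are in the protocol article.

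- **Imaging data analysis** closes with the rule: "MRI data from patients who received the drugs will be excluded because of the effects of the combination on brain function during the trial". It identifies patients, not scans or time points.
- **Multimodal MRI data acquisition** gives patients two scans: "MRI scans will be assessed at baseline and after 4 weeks".
- **Fig. 2 legend** puts the first of these ahead of the intervention: patients "complete clinical and MRI assessments before treatment".
- **Inclusion criteria**, item 4, requires patients at entry to be "not taking any medication or health care products to improve sleep quality"; I read the two-week window in that item as applying to this requirement.
- **Concomitant medication** sets the condition for drug use during the study. If patients' "insomnia symptoms do not significantly improve and they cannot tolerate their insomnia, they may temporarily take sleeping drugs".
- **Study design** gives the controls a single scan: "30 healthy controls (HCs) matched for age, sex, and education level will receive one multimodal MRI scan and a clinical assessment".
- **Discussion** names the use of a patient-control comparison: "We first want to explore neuropathological changes in patients with CID and GI disorder from the perspectives of brain structure, function, and metabolism". The Abstract also gives the pathological mechanism as part of the study's aim.

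Nowhere does the article say that the baseline scans of later drug users are kept.

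**The concern.** The rule reaches further than its own reason. That reason is an effect of combined treatment on brain function while the trial runs. At the baseline scan there has been no acupuncture, hence no combination, and patients entered free of sleep medication. Nothing in the stated rationale calls for that scan to be discarded.

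Discarding it matters for one analysis in particular. Controls are scanned once, so the natural counterpart is the patients' pre-treatment scan. If later drug users are removed, membership of the patient group at baseline depends on what happened in the following four weeks. The contrast would then describe patients who went on to manage without drugs, not the patients enrolled. Randomisation gives no protection, because patients and controls are not randomised to their groups. The argument in the Discussion that a randomised design mostly controls noise from other treatments therefore does not carry over to this contrast.

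**Working it through.** **1. The plan's own figure.** The only calculated figure is 27 per group in Sample size (difference 2.7, SD 3, α 0.05, power 0.9). A two-sided two-sample t test with d = 2.7/3 = 0.9 gives 26.94, so 27; it reproduces. It concerns the PSQI comparison between arms. The article gives no figure for patients against controls.

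**2. Does the reason fit the scan?**

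| Scan | Sleep medication | Acupuncture received | Combination effect possible |
|---|---|---|---|
| Baseline | none, by inclusion criterion 4 | none (Fig. 2 legend) | no |
| After 4 weeks | possible (Concomitant medication) | yes | yes |

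The rule covers both rows; its reason covers only the second.

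**3. Inputs for the size.** From the article: 60 patients, 30 controls. Assumed, because the article does not give them: share taking drugs q = 10, 20, 30%; true patient-control difference 0.65 SD; equal SDs in both groups; one two-sided t test at 0.05.

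**4. Precision.** Patients left: m = 60 × (1 − q) = 54, 48, 42. The standard error in SD units is √(1/m + 1/30). With all 60 it is √(1/60 + 1/30) = 0.2236.

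| q | m | SE | Ratio to 0.2236 | Power at 0.65 SD, no baseline gap |
|---|---|---|---|---|
| 0 | 60 | 0.2236 | 1.000 | 82.0% |
| 10% | 54 | 0.2277 | 1.018 | 80.5% |
| 20% | 48 | 0.2327 | 1.041 | 78.7% |
| 30% | 42 | 0.2390 | 1.069 | 76.5% |

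The difference detectable with 80% power goes from 0.63 SD with 60 patients to 0.65, 0.66 and 0.68 SD.

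**5. Possible selection bias.** Let g be the baseline mean of later users minus that of non-users, in SD. The mean of all patients is the non-user mean plus q × g. The retained patients have the non-user mean. The shift from deleting users is therefore −q × g.

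| q | g = 0 | g = 0.25 | g = 0.5 | g = 1 |
|---|---|---|---|---|
| 10% | 0 | −0.025 | −0.05 | −0.10 |
| 20% | 0 | −0.05 | −0.10 | −0.20 |
| 30% | 0 | −0.075 | −0.15 | −0.30 |

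A positive g here means that users lie further from the controls than non-users do, so the contrast is understated. A negative g reverses the sign and the contrast is overstated. With g = 0.5, power at a true 0.65 SD would be 74, 65 and 54%; with g = 1 it would be 67, 48 and 30%. These last figures are only as good as the assumed g, about which the article says nothing.

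**The case against.** The strongest reply is that the sentence was never meant to touch the patient-control contrast. It stands in a section that speaks of neural response to treatment and of correlations with change, and it follows directly on those correlations. A change score needs both scans, so dropping the pair is natural there, and the stated reason itself points to on-treatment data. The section does not describe a patient-control test at all; that contrast is inferred from the single control scan, the Abstract and the Discussion. Nor is disease pathology among the three numbered aims in the Background, which are efficacy, central response to acupuncture, and correlation with symptom improvement.

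Much of this stands. The authors may well have meant only post-treatment and change data, and the contrast is exploratory. But the text does not limit the rule, and no other section restores the baseline scans. Nor is this a detail left to a fuller document: the article fixes a rule and a reason, and the two do not match.

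A reader might go further and infer that the contrast will be biased towards zero because the worst sleepers drop out, with power falling to as little as 30%. The document does not support that. The trigger for drug use is a course after baseline, and nothing shows that such patients differ beforehand in ALFF, connectivity, cortical thickness, diffusion measures or glutamate. The 30% combines the largest assumed share with the largest assumed gap, and a single t test is a stand-in for the imaging analyses. The idea that the age, sex and education matching would be upset is likewise unsupported; losing some patients need not unbalance those factors.

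**Conclusion.** The point holds as a defect of wording with a real consequence if the rule is applied literally: pre-treatment scans are lost for a reason that cannot concern them, and the baseline patient group is defined by a later event.

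The cost that follows for any drug use at all is lost precision, and it is small: about 2, 4 or 7% in standard error, or at most 5.5 percentage points of power (82.0 − 76.5), on assumed shares of 10 to 30% and an assumed difference of 0.65 SD. Selection bias of q × g is possible and could outweigh this, but it is zero if later users do not differ at baseline, and the article allows neither its size nor its sign to be worked out. The conclusion concerns the patient-control contrast only. Whether excluding drug users is sound in the real-versus-sham imaging comparison is a separate question that this point does not settle.

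**What to change.** In Imaging data analysis, limit the exclusion to post-treatment scans and to the change analyses that use them. Add that the baseline comparison with healthy controls uses the usable baseline scan of every enrolled patient, whatever drugs were taken later.

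This costs one sentence. The baseline scans are part of the schedule in any case, no rule on treatment or medication changes, and the patient-control contrast loses nothing by it. If the narrower meaning was intended from the start, the change only puts it in writing.

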### Patient safety

During treatment, any adverse events (AEs) will be monitored and recorded in the CRFs throughout the trial. Important AEs in this study would be needle-related AEs, such as bleeding, hematoma, dizziness, infection, neurological symptoms, and fainting. Minor AEs will be treated immediately by the attending acupuncturist. For serious AEs, such as the patient experienced syncope during treatment, the researcher should immediately send the patient to the hospital for emergency treatment, and the research team will also pay appropriate financial compensation to the patient. Any unexpected symptoms during treatment must be recorded in the CRF, regardless of their relationship to the study intervention. For all AEs, the researcher should record them in the CRF and report them to the ethics committee. Severe AEs will be reported to the research ethics committee within 48 h

### Patients and public involvement

Patients and the public were not involved in the design and implementation of the study. They were also not asked to advise on the reporting and dissemination of the results.

### Quality control

To ensure the quality of the clinical trial research project and control the risk, CDUTCM will arrange quality supervisors to supervise the intervention process, informed consent forms, case reports, and data records of the study every 3 months. At the same time, an independent quality management team will be set up within the research team to supervise all aspects of the implementation of this project and regularly write monitoring reports.

## Discussion

Acupuncture is a potential therapy for CID. In recent years, some researchers have used MRI to study the neural mechanisms by which acupuncture treats certain types of insomnia, such as perimenopausal insomnia [60] and shift work sleep disorder [61]. However, there have been few reports on the mechanism of acupuncture in treating insomnia and GI comorbidities. Previous studies have found that acupuncture has a good effect on inflammation of GI diseases [16–18], which also provides strong support for the treatment of CID patients with GI diseases with acupuncture. In our protocol, multimodal MRI will be used to explore the pathological mechanism of CID with GI disorder and the main response characteristics of acupuncture therapy for this type of insomnia. There will be several study strengths and limitations.

In the theoretical system of traditional Chinese medicine, insomnia accompanied by GI disorder is a common syndrome. According to the Yellow Emperor’s Canon of Internal Medicine, a famous Chinese medical text, Chinese doctors discovered a link between GI illness and sleep more than 2,000 years ago, and developed the principle of “harmonizing the stomach and mind” [62]. Our acupoint selection protocol is based on this treatment principle, and the selected points DU20, RN12, and ST36 are commonly used acupoints for insomnia associated with GI disorder in acupuncture clinical trials [63]. DU20 improves sleep, and RN12 and ST36 harmonize GI functions. Evidence from clinical trials using the “harmonizing the stomach and mind” principle has confirmed the effectiveness and safety of acupuncture for CID with GI disorder [19, 64, 65]. These acupoints were also presented in a study protocol on the intestinal flora of acupuncture for insomnia and gastrointestinal diseases published by our team [66].

Multimodal MRI will provide technological data to examine the neuropathological mechanism underlying the effect of acupuncture on CID with GI disorder. We first want to explore neuropathological changes in patients with CID and GI disorder from the perspectives of brain structure, function, and metabolism. Our previous study was a preliminary exploration of the pathogenesis of insomnia (rather than CID with GI disorder) in terms of brain function and structure [23, 24, 67]. Other research teams have confirmed that insomnia patients have abnormal brain metabolism using MRS technology [27–29]. At present, there are no brain imaging studies on patients with CID and GI disorders. Most studies on insomnia have identified the abnormal brain regions in CID patients as the anterior cingulate gyrus, hippocampus, thalamus, and other regions [68, 69]; these brain regions also feature in GI imaging studies [70]. It remains to be determined whether the structure, function, and metabolism of these brain regions are also changed in CID with GI disorder. Second, we wish to explore the central response mechanism of acupuncture. There is evidence that acupuncture can regulate the neuroplasticity and functional connectivity of abnormal brain regions in other diseases [31, 71], but most studies have used only a single neuroimaging pattern and cannot fully explain the mechanism of acupuncture. Multimodal MRI provides a new way of exploring the mechanism underlying acupuncture. It can examine the mechanism of action in detail from multiple perspectives, which is a more comprehensive approach than the use of single-mode magnetic resonance technology. At present, multimodal MRI has been used to investigate the effect of acupuncture on depression, chronic fatigue syndrome, and other diseases [72–74]. In this study, we will use multimodal MRI combined with sMRI, fMRI, DTI, and MRS. Of these techniques, sMRI and DTI can detect structural changes in different brain regions, fMRI can explore changes in functional connections between different brain regions, and MRS can detect changes in different brain metabolites.

To improve the reliability of results and reduce bias, we will incorporate the following quality control measures. First, the inclusion and exclusion criteria will be strictly applied and the subject groups will be matched on age, gender, height, weight, and other variables. Second, previous studies have found that left-handers and right-handers show different signals in the left and right hemispheres of the brain when performing certain tasks, with more activation in the left hemisphere of the brain in right-handed people [75, 76]. In China, there are more right-handed people than left-handed people. Considering the differences in functional signals between the left and right sides of the brain caused by handedness, this study will only include right-handed people. Third, a project workshop manual will be developed. All the members of our team will be trained to use related diagnostic standards, methods, and evaluation forms. Acupuncture will be performed by two equally qualified acupuncture physicians who will only perform acupuncture after passing a training trial agreed by the research group. Fourth, during the MRI scanning process, the participants’ physiological and mental state may affect the accuracy of the MRI data results [77]. Therefore, we will use SAS and SDS scales to assess the participants' mental state before MRI scanning. In addition, participants will also be told to stop drinking stimulating foods such as alcohol and coffee the day before the MRI scan. Finally, all the imaging will be performed by the same experienced imaging professional.

Some study limitations must be noted. First, during the study, subjects will be allowed to take sleeping medications if they cannot tolerate their insomnia. We cannot ethically limit patients’ choices, and therefore can only ask patients to follow the study treatment regimen as closely as they can, and to record the name and dose of any medication they take on the CRF. Therefore, medication use may be a confounding factor that affects the results. However, as this is a randomized controlled trial, we believe that any noise caused by other treatments will mostly be controlled. Second, the study will be performed in only one center. The bias inherent in the collection and analysis of magnetic resonance data may be increased if the study were to be conducted in multiple locations. Therefore, given the existing technical conditions, we can only conduct a single-center study.

In summary, this study will investigate the effectiveness of acupuncture therapy for CID with GI disorder. We seek to provide scientific evidence for the mechanism of acupuncture in treating CID with GI disorder using multimodal MRI imaging data on brain structure, function, and metabolism.

